Multiple attempts have been made at evaluating the degree of organ damage and capability to recover function after LT. From the original definition of early allograft dysfunction (EAD) by Olthoff et al. [14, 15], through the model for early allograft function (MEAF) score by Pareja et al. [6] a new category of scores based on the kinetics of multiple parameters have recently emerged. Two scores, one developed in the United States at UCLA (L-GrAFT) [1] and one in Italy from a multicenter cohort (EASE) [2], allow the prediction of early AF with excellent C-statistics. Both were validated on multicentric external populations [16, 17]. L-GrAFT and EASE scores are calculated at day 10 after LT; furthermore, a modification of the L-GrAFT score, calculated at day 7, was subsequently developed and validated [17]. Both scores are also proposed for quantifying the degree of graft recovery in translational studies [18–20]. A synopsis of the characteristics of the different scores is displayed in Table 1. However, the prognostic role of pretransplant graft macrosteatosis, the differences among phenotypic patterns of various transplant types (DBD, DCD, and living donor grafts), as well as the detailed characterization of the dynamics that make retransplantation sustainable or contraindicated have not been investigated [21, 22]. Prospective studies evaluating these endpoints and further mitigation strategies to reduce graft-related risks are still awaited.

**Table 1 Tab1:** Previous scores (object, endpoint, cutoff, number of factors utilized, number of entries, accuracy, discrimination power, strength and limitations)

	DRI (2006) [9]	EAD (2010) [5]	D-MELD (2011) [18]	New ET-DRI (2012) [19]	SOFT (2008) [20]	MEAF (2015) [6]	L-GrAFT (2018) [1]	L-GrAFT (2021) [15]	EASE (2020) [2]
Object of score	Donor quality	Graft quality	Donor–recipient match	Donor quality	Donor–recipient match	Graft recovery	Graft recovery	Graft recovery	Graft recovery
Origin of data	UNOS registry data	3 centers	20 centers	EURO TRANSPLANT registry data	UNOS	Monocentric	1 Center	7 Centers	16 Centers
*N* of patients (developing set)	20,023 1998–2002	297 2004–2005	3281 2002–2009	5723 2003–2007	21,673 2002–2006	1026			
Endpoint	Graft failure	Graft dysfunction	Graft failure/patient death	Graft failure	Patient death	Graft failure	Graft failure	Graft failure	Graft failure

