 Timely prediction of AF is pivotal to identifying patients who may potentially benefit from a rescue retransplant before severe complications develop. When massive cytolysis and clear signs of liver failure occur within the first 2–4 days after LT, the indication for retransplantation is clear. Diversely, the decision to retransplant a patient with a milder degree of AF (also called dysfunction) is more challenging, especially after the first 5–10 postoperative days. AF results from a complex interplay between donor, procurement-related, and recipient perioperative factors, all of which contribute to the severity of the ischemia–reperfusion injury. Conversely, the ability of an allograft to recover from such injury is similarly impacted by numerous perioperative events (e.g., preoperative cardiac ischemic damage, frailty–sarcopenia, graft rejection, drug toxicity, kidney failure, or sepsis), [23–31] many of which are poorly studied. Although L-GrAFT and EASE scores accurately predict AF with excellent discrimination, these existing models have not specifically elucidated the role of perioperative events on the need for retransplantation [1, 2, 17]. Notably, this literature is exclusively based on retrospective, single-center studies which have not considered the center-volume effect, with a limited number of DCD and ECD grafts and no evaluation of the possible mitigation effect of MP technologies [1, 2]. The IMPROVEMENT project was designed to pay particular attention to these shortcomings, to capture and analyze as many of these qualitative and semi-quantitative variables as possible to build a comprehensive model that may meaningfully predict AF and guide treatment decisions regarding retransplantation. The study objectives are detailed in Table 2.

**Table 2 Tab2:** Study objectives

Primary (#1)	To make a snapshot of the liver transplant activity on a global basis
Primary (#2)	To develop new algorithms for the timely prediction of Allograft Failure at 90 and 365 days using a comprehensive prospectively collected dataset based on the current clinical practice of liver transplant centers
Secondary (#3)	To validate the already existing predictive models and the newly developed algorithms on a retrospective cohort of patients from intermediate to high medium-volume transplant centers;
Secondary (#4)	To develop a novel time-based dynamic algorithm, with increasing accuracy from the 3^rd^ to 7^th^ post-operative day;

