Kaplan–Meier curves will be calculated and differences will be investigated through log-rank test.ii.Missing data management.

A. Missing data in the calculation of the area under the curve (AUC) and the slope of the kinetic model will be addressed as follows:Patients who were retransplanted or died before day 10 were excluded from the calculation of the AUC and slope because of the real impossibility to calculate the score which is by definition computed at day 10. The number of this subgroup will be reported in the flow diagram of the patients. These cases will be excluded from the patient population utilized for the development of algorithms. However, these cases will be considered for the calculation of the outcome measures (overall % of AF, % failure at 90 days, % failure at 365 days, length of stay, overall graft survival, and overall patient survival).Patients who have been discharged between day 8 and 10 and do not have the day 10 determination (missing value referring to the day 10 determination of AST or Platelet count or bilirubin). In these cases, the values at day 7 will be used. The number of these cases will be reported in the flow diagram. We are aware that this approach might overestimate the value of the AUC and consequently the score’s value. However, as the number of patients without day-10 data is expected to be small, we believe that the effect will be minimal and not relevant for the purpose of the study.Patients with missing data at day 2, or day 3 will be excluded, being impossible the calculation of the score. Their number will be reported in the flow diagram.Patients with missing data at day 4 will be included. The AUC and the slope will be calculated using the trapezoid method not including day 4. Their number will be reported in the flow diagram.Patients with missing data at day 5 will be included. The AUC and the slope will be calculated using the trapezoid method not including day 5. Their number will be reported in the flow diagram.Patients with missing data at day 6 will be included. The AUC and the slope will be calculated using the trapezoid method not including day 6. Their number will be reported in the flow diagram.Patients with missing data on two consecutive days (day 4 and 5, or day 5 and 6, or day 6 and 7) will be included. The AUC and the slope will be calculated using the trapezoid method not including the two consecutive missing days. Their number will be reported in the flow diagram.Composite missing data (e.g., AST from one day and bilirubin from a different day) will follow the above-mentioned rule. Their number will be reported in the flow diagram.Missing data in the descriptive analysis will be reported. Parameters of interest with percentage of missings higher than 8% will not be reported in tables neither will be considered for further univariate or multivariate analysis.Loss to follow-up.

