## Discussion

This protocol refers to the first global study on liver transplantation outcomes. The study design includes several objectives based on LT practice worldwide, with centers participating in a balanced manner depending on their country’s location and activity. In addition to cross-sectional information, we expect to acquire a large volume of data to develop new models for predicting AF at different time points.

First, it will be paramount to build a new model for predicting early AF (i.e., 90-day post-LT allograft failure) based on a multicenter international comprehensive retrospective and prospective data collection. The work set by the steering committee stands on the background of the existing kinetics-based scores (L-GrAFT and EASE) constructed from a single center and a multicenter two-nation setting, respectively. Compared to these two scores, the models we aim to develop imply the advantage of a wider setting (60 centers, 21 countries, from 6 world areas) and a prospective patient enrollment. In addition to standard transplant outcome measures (graft failure and patient death at 90 and 365 days), we will pay attention to hospital and ITU length of stay, the incidence of weaning/extubation failure [57], as well as surgical complications. [58–60] Furthermore, we expect the study to allow us to develop and validate model(s) with increasing predictive accuracy from the 3rd to 7th postoperative day, making them more usable for all-day practice, bringing forward the availability of prognostic tools in the first few days after LT. We expect these tools to be able to weigh the risk of death without retransplantation and aid the decision-making processes for transplant physicians.

The presence of a retrospective study segment composed of high- and medium-volume centers guarantees a second-layer control of the applicability of previous models as well as the potential backward test of new models to real-world scenarios. The existing kinetic-based scores will be tested on the retrospective data with the aim of validating them on a large scale on a broad variety of liver transplant centers across different countries.

Second, we extended the evaluation time to 365 days, with the intent of capturing those failures occurring at a later stage. Late failure is increasingly seen nowadays due to the growing utilization of DCD and ECD grafts and the subsequent loss of grafts from ischemic cholangiopathy.

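### Failures before day 10 are dropped from algorithm development, so the planned day 3–7 models would be built only on day-10 survivors and would understate early risk

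*Protocol article*

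**What the plan says.** The rule is in the protocol article, Statistical analysis plan, part ii (Missing data management), item A, which opens: "Missing data in the calculation of the area under the curve (AUC) and the slope of the kinetic model will be addressed as follows". Patients retransplanted or dead before day 10 are left out of the AUC and slope "because of the real impossibility to calculate the score which is by definition computed at day 10". The next step goes further: "These cases will be excluded from the patient population utilized for the development of algorithms". They are kept for description: "However, these cases will be considered for the calculation of the outcome measures", and their number goes in the flow diagram.

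The models to be developed are earlier than day 10. Table 2, secondary objective #4, reads "To develop a novel time-based dynamic algorithm, with increasing accuracy from the" third to the seventh post-operative day. The Discussion expects to "develop and validate model(s) with increasing predictive accuracy from the 3rd to 7th postoperative day", "bringing forward the availability of prognostic tools in the first few days after LT". The Introduction also notes that "a modification of the L-GrAFT score, calculated at day 7, was subsequently developed and validated".

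The Outcome measures section defines allograft failure (AF) as retransplant or death from any cause by day 90 and by day 365. A failure on day 6 therefore counts as an event.

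**The concern.** The justification holds for a score computed on day 10: someone whose graft failed earlier was never at risk at that time. It does not hold for a model used on day 3, 4, 5, 6 or 7. A patient at risk on the prediction day who fails before day 10 has the required predictors and is an event the model should learn from. Removing that patient defines the development set by something that happens after the prediction is made.

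Every removed patient is an event, so the mean risk in the development set falls. Discrimination is also estimated in a selected group, without the earliest failures. At the bedside on days 3 to 7 nobody knows who will reach day 10, so the published model would be miscalibrated in the patients it is meant for, and the Discussion wants these tools to support retransplant decisions. If the same exclusion were carried into validation, the observed/expected ratio there would look acceptable and the fault would not show.

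**Working it through.** **Inputs from the article** (Study size and power calculations): overall AF rate 6%; 4,000 patients for the AUC calculation; 800 patients for the calibration calculation; 750 in the prospective segment.

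**The plan's own figures.** With AUC A = 0.76, n1 = 240 events (4,000 × 0.06) and n0 = 3,760 non-events, the Hanley–McNeil variance is [A(1−A) + (n1−1)(q1−A²) + (n0−1)(q2−A²)]/(n1·n0), where q1 = A/(2−A) and q2 = 2A²/(1+A). This gives a 95% interval of 0.724 to 0.796, width 0.072, as printed. The standard error of log O/E is √((1−0.06)/(800 × 0.06)) = 0.140, also as printed. The 6% rate is therefore a fair basis for what follows.

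**Assumptions.** The article gives no timing of failures. Let f be the share of 90-day AF that occurs before day 10, shown from 10% to 40%. Let g be the share of those early failures that occur on or after the prediction day. The value g = 1 means that nobody fails before the prediction day. A later prediction day means a smaller g.

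**Formulas**, with p = 0.06:

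- Risk in the development set under the stated rule: p(1−f)/(1−pf).
- True risk among patients at risk on the prediction day: (p − pf(1−g))/(1 − pf(1−g)). With g = 1 this is p.
- O/E in use is the second divided by the first. With g = 1 it reduces to (1−pf)/(1−f).

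Example, f = 20%, g = 1: 0.048/0.988 = 4.86%, and O/E = 0.988/0.80 = 1.235. With g = 0.5, the true risk is 0.054/0.994 = 5.43%, and O/E = 5.43/4.86 = 1.118.

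| f | Risk in development set | O/E, g = 1 | O/E, g = 0.5 | O/E, g = 0.25 | Events before day 10, of 45 |
|---|---|---|---|---|---|
| 10% | 5.43% | 1.104 | 1.052 | 1.026 | 4.5 |
| 20% | 4.86% | 1.235 | 1.118 | 1.059 | 9 |
| 30% | 4.28% | 1.403 | 1.203 | 1.102 | 13.5 |
| 40% | 3.69% | 1.627 | 1.317 | 1.160 | 18 |

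The last column uses 750 × 0.06 = 45 events in the prospective segment. All of these are removed by the rule; the share wrongly removed is g times the figure shown.

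Against the precision the plan sets itself, f = 20% with g = 1 is a shift of ln(1.235) = 0.211, or 0.211/0.14 = 1.5 standard errors of log O/E.

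**A side effect.** The AUC calculation counts all 240 events. For the day-10 scores the exclusion is right, but those events are then not available. With f = 20%, 192 events remain, the width becomes 0.080 and the lower limit at AUC 0.76 is 0.7198, just below the 0.72 to be excluded.

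**The case against.** The strongest reply is about scope. The sentence sits in an item about the kinetic AUC and slope and follows directly on a remark about a day-10 score, so it may have been meant only for algorithms built on day-10 quantities. In that setting the exclusion is sound. Primary objective #2 gives outcome horizons but no prediction day, so a new day-10 model under it would not be harmed. The sentence concerns development, so it does not settle how existing day-3 or day-7 scores will be validated.

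These limits are fair, but they do not rescue the sentence. EASE and L-GrAFT10 already exist and are only validated here. What the study develops are new algorithms, and the only prediction days fixed for them are days 3 to 7. The wording carries no restriction, and no other at-risk set is given for those models.

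The second reply is about size. The 6% is incidence from transplant, which is the right comparator for a day-k model only if nobody fails before day k, while the Introduction describes clear failures at days 2 to 4. It adds that retransplant is plainly indicated in such cases, so some of the removed patients are not where a model is most needed. A day-7 model also loses far fewer days of failures than a day-3 model. All of this stands and is why the table includes g below 1. It reduces the size and leaves the direction unchanged.

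Third, the excluded patients are counted openly and kept in the outcome description. That is good reporting, but it does not correct a model fitted without them. Nor is this a detail left to a fuller plan: the article states the rule.

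**Conclusion.** The concern holds. As written, the day-10 exclusion governs algorithm development without restriction, and for the day 3–7 models it conditions on later survival. Predicted risk is too low whenever any failure falls between the prediction day and day 10.

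The size cannot be fixed from the article. At 6% AF and with 10% to 40% of 90-day failures before day 10, O/E in use is about 1.10 to 1.63 if all of them follow the prediction day, 1.05 to 1.32 if half do, and 1.03 to 1.16 if a quarter do. These figures are illustrative. The conclusion applies to any model with a prediction day before day 10, which includes objective #4 in terms and objective #2 so far as its models predict that early. The effect on discrimination cannot be signed.

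**What to change.** Replace the single day-10 rule with an at-risk rule tied to each model's prediction day:

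- For a model or score computed on day k (k = 3, 4, 5, 6, 7 or 10), include every patient alive with the first graft in place on day k. Use predictors recorded up to day k, and predict AF from day k to days 90 and 365.
- Exclude only failures before day k, and report their number for each k in the flow diagram.
- Keep the day-10 exclusion for EASE, L-GrAFT10 and any new model computed on day 10. State that L-GrAFT7 and MEAF are assessed in patients at risk on day 7 and day 3.
- Use the same at-risk sets in validation, and base the sample-size statements on events remaining after each prediction day.

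The cost is a change of wording and one analysis set per prediction day. No new data are needed.

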Cutoff and % of predicted at cases	≥ 2 80 % 90 dd	4 75% at 180 dd	Failure: > 1628; 84% at 90 dd Death: > 1628; 86% at 90 dd	> 2 79% at 90 dd	> 40 –	≥ 8 70% at 90 dd	> 1.3 16% at 90 dd	> 1.3 16% at 90 dd	> 0 28% at 90 dd
Evaluation time in relation to LT	Intraoperative (CIT)	7 days	Few hours before LT	intraoperative	Intraoperative CIT	3 dd	10 dd	7 dd	10 dd
Donor	Yes	–	Yes	Yes	Yes	–	–	–	–
Recipient preoperative data	–	–	Yes	–	Yes	–	–	–	Yes
Intraoperative data	–	–	–	–	–	–	–	–	Yes
Transplant logistics	CIT	–	–	Yes	CIT	–	–	–	–
Post-operative data	–	Yes	–	–	–	Yes	Yes	Yes	Yes
Center volume stratification	–	–	–	–	–	–	–	–	yes
Number of variables	8	3	2	8*	19	3	4	4	7*
Total # of determinations	8	3	2	8	19	9	40	27	17
Accuracy at 90 days (derivation set when available)	Not reported	0.72^§^	0.70 and 0.64	0.63	0.69	Not reported	0.85	0.80	0.87
Accuracy at 90 days (validation set or external data set^$^)	0.57^$^	0.63^§$^	0.72 and 0.64	0.58 ^$^	–	0.73 ^$^	0.74	0.74	0.78
Discrimination between highest and lowest risk class					57%	26%			
Strengths	Diffusion		Match oriented		High discrimination	1rst kinetic method	High accuracy high discrimination	High accuracy high discrimination high accuracy in the validation set	High accuracy high discrimination
Limitations	Old, low accuracy, low discrimination		Intermediate accuracy		Intermediate accurac y	Low discrimination	Complexity of calculation (computer)	Complexity of calculation (computer)	Complexity (smartphones/web application) inferior accuracy in the validation set

Abbreviations. $, external data set; §, at 180 days

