#### Study size and power calculations

The study size was calculated to achieve adequate statistical power for the development and validation of prognostic algorithms. Calculations were independently performed by the G-Step Statistical Facility of the Fondazione Policlinico A. Gemelli IRCCS.

*1. Prior knowledge*

1.1. AF incidenceIncidence of allograft failure (AF) at 90 days according to the L-GrAFT study (2018): 11.1% [1].Incidence of AF at 90 days according to the EASE score study: 6.7% [2]—Incidence of EAF according to the L-GrAFT validation study (2020) in UCLA: 7% [17].Incidence of AF at 90 days according to the L-GrAFT validation study (2020) in other US validation centers: 11% [17].Incidence of AF at 90 days according to the L-GrAFT validation study (2020) in European COPE cohort: 4% [17]. Notably, the COPE cohort consists of 222 grafts.

Research hypothesis stratified by donor category:10% AF in liver transplantation with high-risk deceased donors;7% AF in liver transplantation with standard deceased donors;4% AF in liver transplantation with living donors.

1.2. EASE and L-GrAFT score performance as AUC (95% confidence interval)EASE(10) AUC = 0.87 (0.83, 0.91).L-GrAFT10 AUC = 0.72 (0.65, 0.78).L-GrAFT7 AUC = 0.78 (0.75, 0.82).

*2. L-GrAFT and EASE score algorithms validation*

Current target sample size (*n*):5000 transplants overall;> 4125 for the retrospective study.750 for the prospective study.

This estimation aims to provide the minimum sample size to achieve the baseline AUC, considering a different AF incidence for each donor category. The baseline (i.e., lowest) AUC = 0.72 of the L-GrAFT10 score is considered a minimum performance requirement to reach a conservative sample size estimation.

Assuming an overall AF rate of 6% and aiming to exclude an AUC value of 0.72, a minimum sample size of 4000 patients will result in a 95% confidence interval width of 0.072; so, if we obtain an AUC of at least 0.76, the 95% confidence interval, ranging from 0.724 and 0.796, will allow to exclude the value of 0.72.

*3. Dimension of the validation set.*

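### The day-7 fill for a missing day-10 value raises the scores of early-discharged patients, and the claim that the effect is minimal has no figure behind it

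*Protocol article*

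**What the plan says.** The rule stands in the Protocol article, Statistical analysis plan, item ii (Missing data management). It covers "Patients who have been discharged between day 8 and 10 and do not have the day 10 determination", naming AST, platelets and bilirubin, and provides: "In these cases, the values at day 7 will be used". The number of such cases is to appear in the flow diagram.

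The article then comments on its own rule: "We are aware that this approach might overestimate the value of the AUC and consequently the score’s value". It adds that "as the number of patients without day-10 data is expected to be small, we believe that the effect will be minimal". No expected count, percentage or threshold is given.

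Other gaps are treated differently. A single missing day 4, 5 or 6, or a consecutive pair within days 4–7, is skipped; for pairs, "The AUC and the slope will be calculated using the trapezoid method not including the two consecutive missing days". Patients retransplanted or dead before day 10 are left out of the score calculation.

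The rule matters because "L-GrAFT and EASE scores are calculated at day 10 after LT", and validating existing models is secondary objective #3. The discrimination target, set against a reference value of 0.72, is in Study size and power calculations: "if we obtain an AUC of at least 0.76, the 95% confidence interval, ranging from 0.724 and 0.796, will allow to exclude the value of" (the quote stops just before that reference value).

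**The concern.** Four features of the rule are weak on the article's own text.

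- **Inconsistent.** Gaps in days 4–7 are bridged by the trapezoid over observed days; only the day-10 gap is filled with an older value.
- **No exception for later data.** As written, a day-8 or day-9 value, if recorded, is not preferred to day 7.
- **Incomplete.** The section keeps patients with days 6 and 7 both missing, who have no day-7 value to carry. INR, a main parameter in Table 3, is not named.
- **Differential.** Early deaths and retransplants are already excluded, so the fill falls on survivors fit for discharge. The argument for a minimal effect rests on the count alone and ignores this selection.

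At stake is first the level of the day-10 scores. If low-risk patients get scores that are too high, predicted risk is too high at the low end. Second, raising scores mainly among patients who do not fail can cost some discrimination.

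**Working it through.** Below, kinetic area means the area under a marker's curve, and c means the c-statistic.

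**1. The plan's own interval.** Inputs from Study size and power calculations: N = 4000, AF rate 6%, c = 0.76. Events n1 = 240, non-events n0 = 3760. Hanley–McNeil: SE² = [c(1−c) + (n1−1)(P1−c²) + (n0−1)(P2−c²)]/(n1·n0), with P1 = c/(2−c) = 0.6129, P2 = 2c²/(1+c) = 0.6564 and c² = 0.5776.

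SE² = (0.1824 + 239 × 0.0353 + 3759 × 0.0788)/902,400, so SE = 0.0184. The interval is 0.76 ± 1.96 × 0.0184 = 0.724 to 0.796, as stated. The slack above 0.72 is 0.724 − 0.720 = 0.004. The lower limit is 0.7209 at c = 0.757 and 0.7198 at c = 0.756.

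**2. What the fill does to one curve (assumed marker).** Take a marker at 100 on day 7 with a 3-day half-life: 79.4, 63.0 and 50.0 on days 8, 9 and 10. Trapezoid area over days 7–10:

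| Day 7–10 segment | Area | Error |
|---|---|---|
| All days observed | 89.7 + 71.2 + 56.5 = 217.4 | – |
| Day 7 carried flat to day 10 | 3 × 100 = 300 | +38% |
| Days 8 and 9 kept, day-7 value placed at day 10 | 89.7 + 71.2 + 81.5 = 242.4 | +12% |
| Last observed value is day 8 | 89.7 + 2 × 79.4 = 248.4 | +14% |
| Last observed value is day 9 | 89.7 + 71.2 + 63.0 = 223.9 | +3% |

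For half-lives of 2 to 5 days the flat fill errs by +59% to +22%. It also sets the day 7–10 slope to zero. Keeping days 8 and 9 creates a false rebound from 63 to 100.

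**3. What the fill does to discrimination (assumed inputs).** Binormal scores with 60,000 events and 940,000 non-events, c about 0.76. A share q is filled, and filled scores rise by 0.25 or 0.5 SD. The correlation r between a low score and early discharge is 1, 0.5 or 0. In model A, discharge depends on the score alone. In model B, a failing patient who would be filled under A is filled with probability 0.3, the overall share being held at q. None of q, shift, r or 0.3 is in the documents. Loss of c, shown as 0.25 SD / 0.5 SD:

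| q | Model | r = 1 | r = 0.5 | r = 0 |
|---|---|---|---|---|
| 5% | A | 0.0000 / 0.0001 | 0.0002 / 0.0007 | 0.0003 / 0.0012 |
| 5% | B | 0.0001 / 0.0003 | 0.0011 / 0.0025 | 0.0022 / 0.0049 |
| 10% | A | 0.0000 / 0.0002 | 0.0003 / 0.0016 | 0.0005 / 0.0022 |
| 10% | B | 0.0004 / 0.0011 | 0.0025 / 0.0058 | 0.0044 / 0.0097 |
| 20% | A | 0.0001 / 0.0010 | 0.0006 / 0.0030 | 0.0010 / 0.0041 |
| 20% | B | 0.0017 / 0.0046 | 0.0059 / 0.0135 | 0.0088 / 0.0190 |
| 30% | A | 0.0001 / 0.0018 | 0.0010 / 0.0045 | 0.0014 / 0.0056 |
| 30% | B | 0.0042 / 0.0107 | 0.0097 / 0.0220 | 0.0131 / 0.0282 |

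The more closely early discharge follows a low score, the smaller the loss: raising the lowest scores changes few event/non-event rankings. The harshest column is model B with r = 0, where discharge is unrelated to score within outcome groups.

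**4. Slack away from the break-even value.** At c = 0.78, the EASE validation figure in Table 1, SE = 0.0179 and the lower limit is 0.78 − 1.96 × 0.0179 = 0.745, a slack of 0.025.

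**The case against.** The article is open about the limitation. It states the direction of the error, will count the cases and expects few. If the share is 2–5%, the effect on discrimination is small in nearly every scenario. That stands; what is missing is a figure behind the expectation.

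A reader might infer that the study holds day-8 and day-9 values and throws them away, because Table 1 ("Total # of determinations") gives L-GrAFT (2018) 40 for 4 variables, that is 40/4 = 10 per variable. That row describes the published score, not this study's eCRF. The same row gives 17 for EASE without listing days, the missing-data rules name no day 8 or 9, and the variable list is in a supplement not shown. The article does not settle what is collected. The day-7 values could even be meant as input to a day-7 score.

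A reader might also infer that the 0.004 slack leaves the validation no room. But 0.76 is the minimum qualifying value at the minimum sample size, so the slack is small by construction.

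Finally, a condensed article may leave INR handling and sensitivity analyses to the full plan. That is fair for their absence alone. It does not excuse the rule that is stated.

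**Conclusion.** The rule is a poor choice that the article itself says may inflate the score, and its defence is unquantified. The error is differential, so score levels and low-end calibration are the most direct casualty. Discrimination can fall slightly: about 0 to 0.003 at 3–5% filled in most scenarios, 0.005 at worst. Outside the harshest scenario the loss passes 0.004 only at roughly 10% or more filled with a 0.5 SD shift, or about 20% or more with a smaller shift. In the harshest scenario it does so at 5% with 0.5 SD and at 10% with 0.25 SD.

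The stronger reading, that discrimination is materially biased down, is not supported. A loss near 0.028 needs 30% filled, a 0.5 SD shift, discharge unrelated to score and failing patients filled at 0.3 times the rate. All of these are assumptions. The downward direction is plausible, not proven.

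**What to change.** Rewrite the rule as follows.

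- Where a day-8 or day-9 value exists, use the latest observed value instead of day 7.
- Where nothing exists after day 7, report the day-7 score rather than a filled day-10 score. Table 1 lists a day-7 version for L-GrAFT only, so say how EASE is handled.
- Apply the same rule to INR where a score uses it, and state what happens when day 7 is missing too.
- Report discrimination and calibration of the day-10 scores also in patients with an observed day-10 value. These patients are themselves selected by longer stay, so this stands beside the main analysis and does not replace it.
- Keep the day-7 carry-forward as a sensitivity analysis, and replace the statement that the effect is minimal with the observed share filled and the difference between the two analyses.

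The cost is a few lines of wording, a little more programming and one extra analysis run. No new samples are needed.
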